### ● Data management

Data are coded and processed with Research Electronic Data Capture (REDCap), a broadly used HRA-compliant data collection application [31, 32]. Data will be archived in coded form for a minimum of 10 years after study completion.

### ● Safety considerations

To date, in the literature, the only recognized side effect of virtual reality is cybersickness [16], a condition similar to motion sickness but caused by immersion in virtual reality rather than by actual movement.

The prevalence of cybersickness is not known because of the diverse software and hardware that deliver virtual reality.

The manufacturer of the Oncomfort system also warns the users of the potential risks of:

claustrophobiaproblems with orientationsweating of the facesleepiness

The prevalence of the above risks is not known.

The present study intends to compare vascular radiologic interventions with or without a virtual reality mask with a specific program to release stress and tension from patients undergoing certain procedures.

We will collect device deficiencies and adverse events, including all serious adverse events. Adverse events will be thoroughly investigated and documented in the medical record and the case report form (CRF) during the entire study period.

There is no follow-up period needed for this study since virtual reality has no known long-term adverse effect.

### ● Type of data and statistical analyses

Quantitative discrete data will be the Spielberger anxiety state self-questionnaire results, rated visual analog pain scale, age, the amount of drugs administered for pain and anxiety. We will compare the means of the discrete quantitative data with two-sided student tests.

Qualitative data are participants that did not tolerate the mask before randomization, participants that had to take off the mask, and the occurrence of cybersickness. We will compare the occurrence of qualitative data between both groups with the Wilcoxon signed-rank test.

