### ● Sample size, inclusion, and exclusion criteria

A power analysis was conducted to determine a sample size that can detect a statistically significant anxiety decrease of at least 5 percent, such as encountered in a previous investigation using autohypnosis in the setting of systemic chemotherapy [29]. The Sample size calculation is based on the primary outcome "per procedural anxiety". The expected mean (sd) of per procedural anxiety in the control group is 45 (3) and 5% lower in the intervention group 42.75 (2). The minimum sample size needed to show that the mean difference is significant with a power of 90% and an alpha of 5% (two-sided) is 32 patients per group. To avoid loss of power due to possible dropout (20%), randomizing 40 patients in each group would be appropriate. Furthermore, because the primary outcome measure is patient-reported and subject to measurement error, we intend to add a safety margin and include 50 participants in each group since no additional risk nor financial burden is associated with study participation.

Inclusion criteria: participants will be patients subjected to interventional radiology for a peripheral vascular intervention under local anesthesia; participants will be over 18 years old and have signed an informed consent form. In this study, peripheral EVI refers to lower limb arterial angioplasty and stenting, renal and mesenteric angioplasty and stenting, venous interventions (vena cava filter placement, venous malformation embolization, peripherally inserted central catheter). Patients referred to cardiothoracic or neuroradiology intervention are not eligible.

Exclusion criteria: no or limited study language comprehension, deafness or visually impaired patient, the anticipated need for a sedative medication, a history of motion sickness or a psychiatric disease such as paranoia, schizophrenia, deep water phobia, and dementia. We will also exclude patients who do not tolerate the virtual reality mask during a preoperative visit.

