### ● Characteristics of participants, randomization, and blinding

The sequentially numbered, opaque, sealed envelope (SNOSE) method was used for randomization with a 1:1 allocation before the intervention. A person not involved with patient recruiting will print the allocation sequence and prepare the envelopes ([name]).

One group of participants will wear the virtual reality mask with the autohypnosis program running during the EVI. The other group will benefit from the intervention in standard conditions without the virtual reality mask.

The study will run in an open-label fashion because information cannot be withheld from trial participants and operators. Participants included in the virtual reality arm will wear the head-mounted device, and awareness regarding self-hypnosis is inevitable.

Study timetable: the first patient was included in August, 2020. The recruitment is expected to be completed by the end of May, 2022.

All vascular punctures are performed under local anesthesia and using ultrasound guidance. The puncture site depends on the clinical indication and is at the operator’s discretion. The typical vascular access is the common femoral artery for peripheral and visceral arterial interventions. The most common venous accesses are the common femoral vein and brachial veins.

Arterial vascular accesses usually benefit from vascular closer devices, at the operator’s discretion, while venous accesses are controlled by manual compression.

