### ● Processes, interventions, and comparisons

The schedule of enrolment, interventions, and assessment is presented in Fig 1. On the day of the intervention, after randomization, the participants will fill the operative anxiety self-questionnaire (Table 1) and indicate the intensity of pain felt on a segmented numerical version of the analog visual scale (Table 2). At the patient’s arrival in the operating room, an investigator will adapt the virtual reality mask if the patient is in the virtual reality group.

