## ● Measured outcomes

The primary outcome is the rated per procedural anxiety, measured by the Spielberger Anxiety State Inventory in French [30]. The Spielberger Anxiety State Inventory is a self-questionnaire of 20 items, each item scores from 1 to 4. The test result is the sum of the 20 items; therefore, the results range from 20 to 80 (Table 1). A high score is related to a high level of anxiety at the moment of the test.

The secondary outcome is the rated per procedural pain measured by the visual analog pain scale. The visual analog pain scale rates pain from 0 to 10, 0 being no pain, and 10 being the worst pain imaginable (Table 2).

Both outcomes will be measured on day 1, before and after the intervention, and 3 months after the intervention.

The other outcomes of interest will be measured on day 1. Those outcomes are age and sex, side effects of virtual reality, the amount of drugs administered for pain and anxiety, the number of participants that did not tolerate the mask before randomization, and the number of participants where the mask has been taken off (patient decision/medical team decision). We will measure the prevalence of cybersickness, our safety outcome on day 1.

Patient-relevant outcomes, including amputation, mesenteric or renal ischemia, and death, will be reported 90 days after EVI.

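### The anxiety score is compared by an unadjusted t-test, which is valid but leaves precision unused; the pre-procedure score is a safe covariate only if taken before allocation is known

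*Protocol article*

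**What the plan says.** The section on type of data and statistical analyses lists the anxiety questionnaire, the pain scale, age and drug amounts as quantitative data, and then states: "We will compare the means of the discrete quantitative data with two-sided student tests". It names no covariate. It also does not say whether the post-procedure score or the change from before the procedure is compared.

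The material for an adjusted analysis is largely there. Under measured outcomes, on anxiety and pain: "Both outcomes will be measured on day 1, before and after the intervention, and 3 months after the intervention". Eligibility covers lower-limb, renal and mesenteric angioplasty and stenting as well as "venous interventions (vena cava filter placement, venous malformation embolization, peripherally inserted central catheter". Allocation is 1:1 by sealed envelope, and no stratification is mentioned.

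Two further statements limit what can be done with the pre-procedure score. Under processes, interventions and comparisons: "On the day of the intervention, after randomization, the participants will fill the operative anxiety self-questionnaire (Table 1". Under randomisation and blinding: "The study will run in an open-label fashion because information cannot be withheld from trial participants and operators".

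Procedure type is not in the list of other day-1 variables, which begins: "Those outcomes are age and sex, side effects of virtual reality, the amount of drugs administered for pain and anxiety" and goes on to mask tolerance and mask removal.

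**The concern.** A state anxiety score taken shortly before the procedure will usually predict the score reported shortly after it. The type of procedure may do so too: a catheter insertion and a mesenteric stent are different experiences. A t-test on means leaves all of that variation in the error term. A linear model with a properly timed pre-score and a procedure-group term would remove some of it at almost no cost.

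What is at stake is the width of the confidence interval for the primary outcome, and power if patients vary more than the design assumes. The assumed SDs are 3 and 2 points on a scale that runs from 20 to 80. There is a second, smaller stake. Because the text does not say whether the post-procedure score or the change is compared, the choice among post-score, change score and adjusted score could be made after results are seen.

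**Working it through.** **Inputs from the article (sample size section).** Control mean 45, SD 3; intervention mean 42.75, SD 2; difference 2.25; two-sided 5%; 90% power; 32 per group, 40 after 20% dropout, 50 planned.

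**Assumed inputs, not in the article.** Pre/post correlation r = 0.4, 0.5, 0.6; alternative SDs of 5 and 8; a 1-point shift of the pre-score (step 5).

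**1. The plan's own figure.** Pooled SD = √((3² + 2²)/2) = √6.5 = 2.55. The n per group for 90% power is 27 (normal approximation), 28 (exact t) or 29 (Welch), not 32. The stated 32 gives 93.5% power, so it errs on the large side. That mismatch is a separate matter. The dropout step, 32/(1 − 0.20) = 40, reproduces.

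**2. Unadjusted power on the protocol's SDs.** SE = 2.55 × √(2/n), which is 0.570 at n = 40 and 0.510 at n = 50. The noncentral t gives 97.4% and 99.2%.

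**3. Effect of adjusting for a clean baseline.** Residual variance = SD² × (1 − r²).

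| r | Variance removed (r²) | Equivalent extra patients, 1/(1 − r²) − 1 |
|---|---|---|
| 0.4 | 16% | 19% |
| 0.5 | 25% | 33% |
| 0.6 | 36% | 56% |

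**4. Power for a difference of 2.25**, from the noncentral t with SD × √(1 − r²).

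| SD | n per arm | t-test | r = 0.4 | r = 0.5 | r = 0.6 |
|---|---|---|---|---|---|
| 2.55 (protocol) | 40 | 97.4% | 98.9% | 99.5% | 99.8% |
| 2.55 (protocol) | 50 | 99.2% | 99.8% | 99.9% | >99.9% |
| 5 (assumed) | 40 | 51% | 58% | 63% | 70% |
| 5 (assumed) | 50 | 61% | 68% | 73% | 80% |
| 8 (assumed) | 50 | 29% | 33% | 36% | 41% |

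On the protocol's SDs the gain is at most about 2.4 percentage points. At SD 5 it is worth having. At SD 8 it does not rescue the design.

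**5. What the timing of the pre-score can do.** Suppose that knowing the allocation lowers the pre-score by 1 point in the mask arm. With equal pre and post SDs the regression slope is r, so the adjusted effect is 2.25 − r × 1 = 1.85, 1.75 and 1.65 for r = 0.4, 0.5 and 0.6. The shift also inflates the variance slightly, by 1 + (1/SD)²/4, which is 1.01 at SD 5. At SD 5 and 50 per arm, power becomes about 51%, 51% and 53%, below the unadjusted 61%. On the protocol's SDs with 40 per arm, the same shift gives 93% to 94% against 97.4%. A shift in the other direction would inflate the adjusted effect instead.

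**The case against.** **The t-test is valid.** This stands. A reader might infer that omitting covariates makes the primary analysis wrong; it does not. Nor does the absence of stratification bias the t-test. Chance imbalance in procedure mix or baseline anxiety is already counted in its standard error, and should not be presented as a further error on top of it.

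**Adjustment is commonly left to an analysis plan, which is not shown.** This stands only in part. The article does not leave the method open: it fixes a test for these outcomes.

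**The pre-procedure score is not a clean baseline.** This is the strongest objection, and it stands. A reader might infer that adjusting for it estimates the same effect with a smaller standard error. That holds for a covariate measured before randomisation. Here the questionnaire comes after randomisation in an open-label trial, so it may already carry part of the effect of allocation. The article does not say when each patient learns the allocation, so a shift is possible rather than shown. An adjusted model as the sole primary analysis under the current order could be worse than the t-test.

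**Procedure type is not listed as recorded.** Correct, so its availability is an inference. It is a fair one, because eligibility is defined by procedure and the clinical record must show it. Procedure is set by clinical indication, so adjusting for it should not carry the timing problem.

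**The size of the gain rests on assumptions.** Correct. Neither the correlation nor the between-procedure variance is in the article.

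**Conclusion.** The point holds as a matter of efficiency and pre-specification. The protocol fixes an unadjusted comparison and makes no use of the pre-procedure score or the procedure type. If the pre-score is clean and its correlation with the outcome is 0.4 to 0.6 (assumed), 16% to 36% of the residual variance could be removed. On the protocol's own SDs this hardly matters, with power already at 97% to 99%. Its value is partial insurance if the SD is larger: at an assumed SD of 5 with 50 evaluable per arm, power rises from 61% to between 68% and 80%.

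The benefit depends on timing. For patients who complete the questionnaire knowing their allocation, the documents do not support treating the pre-score as a baseline, and an assumed 1-point shift is enough to turn the gain into a loss. The change is worth making, but in a form that respects this. The planned analysis is not invalid without it.

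**What to change.** 1. For patients still to be enrolled, have the pre-procedure anxiety and pain scales completed before the envelope is opened. Record the order for every patient.
2. Before results are seen, pre-specify a linear model of the immediate post-procedure score on arm and procedure group (arterial / catheter insertion / other venous), with procedure group taken from the clinical record. Add the pre-procedure score only where it was taken before allocation was known. Use the same approach for pain.
3. For patients scored after allocation, keep the analysis without the pre-score as primary and show the pre-score-adjusted model as a sensitivity analysis. If both kinds of patient are present, one model can serve: include an indicator for questionnaire order, and enter the centred pre-score for those scored before allocation and zero for the rest.
4. Report the adjusted difference with its 95% confidence interval, and the t-test alongside. State that the outcome is the post-procedure score, not the change.

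Cost: a small change in the order of study procedures, which is more than analysis wording and cannot be applied to patients already enrolled; one field on the case report form for procedure type; and two degrees of freedom for procedure group, one for the pre-score, and one more if the order indicator is used.

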## Materials and methods

### ● Aim, design, and setting of the study

This prospective study is based in a single Swiss academic hospital and seeks to evaluate whether virtually augmented self-hypnosis (VA-HYPO) lowers anxiety and pain in the setting of percutaneous peripheral and visceral arterial and venous EVI. VA-HYPO is performed using a head-mounted device (Oncomfort^TM^) providing a video screen and sound system aiming to achieve digital sedation. For this study, patients follow the "Aqua" module reproducing a scuba diving experience and breath exercises in a virtual reality environment. For this purpose, a monocentric open-label prospective randomized trial with two arms is designed.

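### A paired test (Wilcoxon signed-rank) is named for yes/no outcomes in two independent arms, and the three outcomes listed do not support a between-arm comparison

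*Protocol article*

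**What the plan says.** The protocol article, section Type of data and statistical analyses, lists three yes/no variables: "Qualitative data are participants that did not tolerate the mask before randomization, participants that had to take off the mask, and the occurrence of cybersickness". It then assigns the test: "We will compare the occurrence of qualitative data between both groups with the Wilcoxon signed-rank test".

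Four other places in the article bear on this.

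- Aim, design, and setting: "a monocentric open-label prospective randomized trial with two arms is designed". No crossover or matching is described.
- Characteristics of participants, randomization, and blinding: the sealed-envelope "method was used for randomization with a 1:1 allocation before the intervention". For controls, "The other group will benefit from the intervention in standard conditions without the virtual reality mask".
- Sample size, inclusion, and exclusion criteria: "We will also exclude patients who do not tolerate the virtual reality mask during a preoperative visit".
- Safety considerations: cybersickness is "a condition similar to motion sickness but caused by immersion in virtual reality rather than by actual movement", and its frequency is said to be unknown.

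The Measured outcomes section names cybersickness as the safety outcome, to be measured as a prevalence on day 1. It lists both mask outcomes as numbers of participants.

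**The concern.** There are two separate problems.

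The first is the test. The signed-rank test ranks differences within pairs. Patients in two parallel randomised arms form no pairs, so it could be run only by matching patients across arms by some rule the plan does not give. The sentence expressly describes a comparison of the two groups, so it cannot be read as a before-and-after analysis within patients. If the rank-sum test was meant, the text still names the wrong one.

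The second is the comparison. For each listed variable, one arm or both cannot sensibly contribute events. Changing the name of the test would leave this in place.

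At stake is the only inferential method stated for the declared safety outcome and for the two tolerability outcomes. The useful result here is how often these events occur under the mask, since the article itself says the frequency of cybersickness is unknown. A p-value against an arm that is effectively at zero does not answer that.

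**Working it through.** **No figure to reproduce.** The article gives no expected rate, power or sample size for these outcomes. The event counts below are assumptions chosen for illustration. The arm size of 50 is the article's planned number per group.

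**Step 1: can each outcome occur in each arm?**

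| Variable | Mask arm | Control arm | Reason |
|---|---|---|---|
| Intolerance found before randomisation | no | no | exclusion criterion, so these patients are never randomised |
| Mask taken off | yes | no | no mask during the procedure |
| Cybersickness on day 1 | yes | not expected | described as caused by immersion; controls are not immersed during the procedure |

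**Step 2: what would the stated test return with controls at zero?** Take k events in the mask arm, none in controls and equal arms. Under any pairing there are k non-zero differences, all of the same sign and size. The zero differences drop out, and the exact two-sided p-value is 2 × 0.5^k (capped at 1). Fisher's exact test is shown for comparison. The last column is the Clopper-Pearson interval for the mask arm alone, with limits at the 0.025 quantile of Beta(k, n−k+1) and the 0.975 quantile of Beta(k+1, n−k). For k = 0 the upper limit is 1 − 0.025^(1/50) = 0.071.

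| Mask-arm events (controls 0/50) | Signed-rank, exact p | Fisher p | Mask-arm proportion (exact 95% CI) |
|---|---|---|---|
| 0/50 | no non-zero differences | 1.0 | 0% (0–7.1%) |
| 3/50 | 0.25 | 0.242 | 6% (1.3–16.5%) |
| 5/50 | 0.0625 | 0.056 | 10% (3.3–21.8%) |
| 6/50 | 0.031 | 0.027 | 12% (4.5–24.3%) |
| 10/50 | 0.0020 | 0.0012 | 20% (10.0–33.7%) |

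**Step 3: does that p-value inform on prevalence?** 2 × 0.5^k contains no denominator. With the article's 20% dropout, an arm of 50 becomes 50 × 0.8 = 40. Five events then give p = 0.0625 in both cases, although 5/50 is 10% (3.3–21.8%) and 5/40 is 12.5% (4.2–26.8%). The interval carries the information; the p-value does not.

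**Step 4: does the computing option matter?** With k tied differences, the normal approximation without continuity correction gives z = √k. At k = 4, z = 2 and p = 0.046, against an exact value of 2 × 0.5^4 = 0.125. The same four events fall on either side of 5% depending on the option used, which the sentence does not fix.

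**Step 5: what if an outcome occurred in both arms?** Only then does arbitrary pairing change the result. Assume 10/50 against 3/50, with o pairs in which both members have the event. The discordant pairs split as 10 − o against 3 − o, and the test becomes an exact sign test. For o = 0 (10 against 3), p = 0.092. For o = 3 (7 against 0), p = 2 × 0.5^7 = 0.016. Fisher's exact test, which needs no pairing, gives 0.071.

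**The case against.** The case for leaving this alone has four parts.

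**The p-value would be harmless.** A reader might infer that the stated test is uncomputable, or an artefact of how patients are paired. For these variables the article does not support that. With controls at zero, equal arms and at least one event, the test can be computed, does not depend on pairing and lies close to Fisher's (0.0625 against 0.056 at five events). Pairing matters only if controls have events, and complete pairs fail only if the arms end unequal. This part stands. It removes the claim of an arbitrary result, but not the mismatch of test and design or the uninformative question.

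**The control rate may not be zero.** A reader might infer that cybersickness in controls is zero by construction. That is slightly too firm. The exclusion criterion implies that candidates, including later controls, try the mask at a preoperative visit, and Measured outcomes places pre-randomisation intolerance on day 1 along with cybersickness. The article does not say whether the program runs at that visit. Some brief exposure of controls is therefore possible. It would precede randomisation, though, and would not make a paired test suitable.

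**An analysis already exists.** A reader might infer that the safety outcome has no valid analysis at all. Measured outcomes already plans a prevalence and counts, and these would be correct whichever test was named. The choice of interval may properly sit in a fuller document that is not shown, so its absence here is not the fault. The fault is the comparison that is stated.

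**Nothing important depends on it.** Anxiety and pain are compared with Student tests, and the sample size rests on anxiety alone. This is correct and limits the severity.

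**Conclusion.** Wrong as written, and it should be fixed. A paired test is assigned to independent groups, and none of the three listed variables supports a meaningful between-arm comparison. One has no arm, one cannot occur in controls, and one is not expected in controls beyond any preoperative try-out of the mask.

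The extent is all three listed qualitative variables, including the declared safety outcome. The primary (anxiety) and secondary (pain) analyses and the sample size are untouched. No numerical bias can be stated, because the article gives no expected rates; the counts used above only illustrate.

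The conclusion assumes that cybersickness is recorded as the article describes it, that is, as a consequence of immersion. If symptoms such as nausea or dizziness were instead recorded in the same way in both arms, a comparison would make sense and only the choice of test would be wrong. Nor does the criticism extend to the 90-day events: the article says only that these will be reported and assigns them no test.

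**What to change.** In Type of data and statistical analyses:

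1. Delete the signed-rank test.
2. Report cybersickness and mask removal as proportions of the mask arm, each with an exact 95% confidence interval.
3. Report pre-randomisation intolerance as a screening result: the number intolerant out of all patients who tried the mask.
4. Reserve a test for two independent proportions, such as Fisher's exact test, for any binary outcome that is recorded in the same way and can occur in both arms.

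The cost is wording only. Sample size, randomisation and trial conduct do not change. Item 3 needs the number of patients who tried the mask, as its denominator. The article describes the trial as still recruiting with no interim analysis planned, so the text can be corrected before the data are analysed.
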